### Setting

The SCORE-Peds project spans a diverse set of care delivery environments across three major regions—Peaks, Canyons, and Desert—covering ~ 250 sites in the intermountain west (see Fig. S3). These settings include pediatrics clinics, family medicine clinics, urgent cares, emergency departments and telehealth. Site locations are also diverse and include urban areas (e.g., Salt Lake City, Utah; Denver, Colorado) as well as rural and suburban areas.

### Inclusion and exclusion criteria

Patients will include children aged 6 months to less than 18 years who were diagnosed with and treated for one of four common acute respiratory tract infections (ARTIs): acute otitis media, Group A Streptococcal (GAS) pharyngitis, acute sinusitis, or pneumonia. Children whose records include penicillin allergies will be excluded from evaluation.

### Study procedures

This evaluation will use observational and quasi-experimental designs to examine effectiveness and implementation outcomes as outlined below. The implementation will proceed in two waves with approximately half of the sites in each wave. To maximize efficiency and likelihood of adoption, sites will be assigned to waves based on region rather than by randomization (see Fig. 2). The first wave includes all sites in the Canyons region with Peaks and Desert regions in the second wave. Each wave will provide a pre-post design using archival baseline data. In addition, the Peaks and Desert regions serve as a comparison group for the Canyons implementation to compensate for possible secular trends. We plan to examine adherence rates overall (aim 1), across sites (aim 2), and as a function of response to Boost (aim 3).

In addition, we plan to examine the use of implementation strategies overall (aim 1), across sites (aim 2), and in response to Boost (aim 3). This examination is based on several key indicators including: the number and frequency of trainings, attendance at trainings, and the frequency with which providers and sites access tools such as EMR utilities (e.g., preference lists, order sets, smart sets), c-SMART dashboards, and audit & feedback reports. We expect that the use of these strategies will vary by site and correlate with changes in adherence.

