**Methods:**

This study will evaluate the implementation of guideline-concordance prescribing for Acute Respiratory Tract Infections (ARTIs) in children 6 months to less than 18 years of age in ~ 250 sites across 5 care specialties (pediatrics, family medicine, urgent care, emergency department, and telehealth). The evaluation will focus on: (1) the overall effectiveness of implementation strategies at driving adherence to guideline-concordant care across the organization, (2) the nature of variability in strategy implementation and adherence by context (e.g., specialty, rurality, region), and (3) the utility of a more intensive implementation, termed “Boost,” for sites with lower adherence after general implementation. Primary effectiveness outcome is adherence to guideline-concordant antibiotic *selection.* Secondary outcomes include adherence to guideline-concordant antibiotic prescription *duration*, and the combination of *both selection and duration* termed Recommended Antibiotic and Duration Adherence Rate (RADAR). We will employ an observational, quasi-experimental approach comparing adherence before and after implementation in two waves across the organization and pre-post Boost for sites selected for intensive implementation support. In addition, we will investigate the correlations between use of implementation strategies and changes in adherence.

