##### Hypothesis

Use of implementation strategies (i.e., engagement) will correlate with changes in adherence.

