#### Aim 3: Assess the impact of Boost on effectiveness and implementation outcomes

##### Rationale

The project includes an exploratory aim to test “Boost” – a more intensive implementation support program akin to academic detailing with sites that are less responsive to initial general implementation and therefore have lower rates of adoption. This allows for comparison of foundational vs. enhanced strategies and focused resource utilization.

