##### Hypothesis

Sites with lower adoption rates who receive the Boost will demonstrate increased use of implementation strategies and increased adherence compared to sites that did not receive Boost.

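### Aim 2 judges engagement by a correlation across sites with change in adherence, but Boost and regional waves can push that correlation either way when engagement has no effect

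*Protocol article*

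**What the plan says.** The Protocol article states the Aim 2 criterion three times:

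- Aim 2, Hypothesis: "Use of implementation strategies (i.e., engagement) will correlate with changes in adherence".
- Study procedures, at site level: "We expect that the use of these strategies will vary by site and correlate with changes in adherence".
- Abstract, Methods: "we will investigate the correlations between use of implementation strategies and changes in adherence".

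The engagement indicators mix counts with rates: "the number and frequency of trainings, attendance at trainings, and the frequency with which providers and sites access tools".

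Boost is described in the Abstract as being "for sites with lower adherence after general implementation". The Aim 3 Rationale describes it as support "with sites that are less responsive to initial general implementation and therefore have lower rates of adoption". The Aim 3 hypothesis expects it to move exposure and outcome together: "Sites with lower adoption rates who receive the Boost will demonstrate increased use of implementation strategies and increased adherence".

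Study procedures puts all Canyons sites in the first wave and all Peaks and Desert sites in the second, without randomization. Data collection and analysis lists age, diagnosis, provider specialty and care setting as covariates. Rurality, race, ethnicity and language are optional. Site baseline adherence, wave and Boost status are not listed.

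**The concern.** A correlation between engagement and change in adherence says something about engagement only if sites with more and less engagement would otherwise have changed alike. The plan's own design works against this in two ways.

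- **Boost.** It is given because adherence is low, and it adds engagement. Any reason why Boost sites change more or less than other sites therefore enters the correlation. If Boost works through detailing and not through the counted tools, it is a common cause of both variables, and Aim 2 partly restates Aim 3.
- **Wave.** First-wave sites come from one region and start earlier. If engagement is a cumulative count and adherence keeps rising, both are larger in that wave.

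Aim 2 also asks which strategies are most effective at driving high adherence, and the article means its findings to inform other health systems. A misleading sign in either direction would carry into that advice: strategies could be recommended, or dismissed, because of how sites were selected.

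**Working it through.** **The plan's own figure.** The article gives no number for Aim 2. Its only power statement (above 99% for an improvement of at least 5%, 356,000 encounters, alpha 0.05) concerns the overall comparison. It reproduces: with 178,000 encounters per period and an assumed 50% baseline, SE = sqrt((0.50×0.50 + 0.55×0.45)/178,000) = 0.00167, so z = 0.05/0.00167, about 30. It has no bearing on Aim 2.

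**Why the sign is open.** Write a site's engagement as E = R + kB + cW. R is unrelated to adherence (the null), B = 1 for Boost sites and W = 1 for wave 1. Then, treating B and W separately,

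cov(E, change) = k·q(1−q)·D_B + c·p(1−p)·D_W,

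where D_B and D_W are the differences in mean change (Boost minus other sites, wave 1 minus wave 2). With q = 0.25 (assumed) and p = 0.5 (about half the sites per wave), the weights are 0.1875 and 0.25. The sign follows D_B and D_W, and the plan does not determine either.

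- D_B is positive if low sites have more headroom. With mean 72%, SD 0.6 logit and a common gain of 0.3 logit (all assumed), a site one SD below the mean goes from 58.5% to 65.6% (about 7 points). A site one SD above goes from 82.4% to 86.4% (about 4 points).
- D_B is negative if sites are low because they responded poorly, which is how the Aim 3 Rationale describes them.
- D_B is near zero if every site gains the same number of percentage points.

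**Null simulation, Boost targeting only.** 250 sites (from the article). Assumed: 300 encounters per site-period, the logit inputs above, the lowest quarter on early post-implementation data receiving Boost, Boost adding 2 SD of engagement and nothing to adherence, change measured from baseline. Ranges cover separate runs.

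| Site gains | Mean r | Significant at two-sided 5% |
|---|---|---|
| Common 0.3 logit | +0.17 | 73 to 77% positive |
| Varying, SD 0.2 logit | 0.00 | no net bias |
| Varying, SD 0.3 logit | -0.11 to -0.12 | 44 to 46% negative |
| Varying, SD 0.4 logit | -0.19 to -0.20 | 88% negative |
| Common 5 points | about 0 | about 5% |

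**Change window.** A second null simulation worked on the percentage-point scale. Assumed: mean 70%, SD 10 points, 100 or 300 encounters per site-period, Boost adding 1 SD of engagement, site drift SD 0 or 5 points. Boost targeting only; nominal 2.5% significantly positive:

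- Baseline to final period: r -0.06 to 0.00; 0.3 to 3.2% positive.
- Baseline to whole post period: r -0.08 to -0.04; at most 0.5% positive.
- Boost-selection period to final period: r +0.01 to +0.10; 3 to 34% positive (regression to the mean).

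**Wave only.** With count-type engagement (wave 1 higher by 0.5 SD) and a trend of 2 points per year, baseline to final gave 6 to 19% positive. With twice the accumulated count in wave 1 and a further gain of 0.10 to 0.15 logit or its point equivalent, it was 65 to 97%. With engagement as a rate, or with no later gain, rejection returned to 5.5% and 4.5% (two-sided 5%).

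**Boost as common cause.** If Boost raises adherence by 0.15 to 0.3 logit (or the point equivalent) by routes other than the measured indicators, 61 to 99% of runs were significantly positive.

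**With adjustment.** Pre-Boost engagement rate, adjusted for baseline adherence and wave, rejected in 3 to 7% of null runs (two-sided 5%) in every scenario tried. Conditioning full-period engagement on wave, Boost status and baseline adherence gave 1.2 to 4.3% significantly positive (nominal 2.5%).

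**The case against.** The strongest reply has four parts.

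- **The article never says raw or unadjusted.** It says only that engagement will correlate with changes in adherence, it describes covariate-adjusted models for the analyses in general, and the estimator may sit in an analysis plan not shown. This stands. A reader might infer that a crude Pearson correlation is prescribed, and the text does not support that. But if the listed covariates are carried over to Aim 2, they still leave out baseline adherence, wave and Boost.
- **The direction is not fixed.** A reader might infer that a positive correlation will appear and the hypothesis will be reported as supported. The documents do not support this. Targeting less responsive sites can work against the hypothesis, and a common gain in points gives no bias. With both mechanisms active, count engagement, a 0.15 logit later gain and site-gain SD 0.3, rejection was only about 8%.
- **The wave effect needs conditions the article does not state:** a common data cut, cumulative counts and continuing gain. This stands; several of the listed indicators are frequencies.
- **The limits are disclosed.** Challenges and limitations says that non-randomized waves and Boost selection weaken causal inference and that the study is not a rigorous test of specific hypotheses. That is a fair general caveat. It does not say that Boost allocation feeds Aim 2's exposure, and it does not change the analysis.

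**Conclusion.** The concern holds as a bias of undetermined direction. Boost is allocated on adherence and is expected to raise engagement, wave coincides with region, and no listed covariate addresses any of this. A correlation pooled across sites therefore cannot by itself judge the Aim 2 hypothesis. With no effect of engagement and Boost targeting alone, results ran from 88% significantly negative to 77% significantly positive. The sign turned on how site gains vary and on where the change window starts; whether engagement is a count or a rate decides whether wave adds to it. Apart from the number of sites and the rough half-and-half wave split, every simulation input is assumed, so these figures show how far the result can move and do not predict it. The point should be corrected; it does not affect the primary outcome.

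**What to change.** State that the Aim 2 hypothesis is judged by a site-level regression:

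- **Outcome:** adherence to selection in a fixed window after each site's own three-month rollout period, the same length in both waves and closing before Boost starts. The figure with the timetable is not visible, so the sponsor must set the length.
- **Exposure:** engagement per unit time (for example per prescriber-month) accrued before Boost selection.
- **Adjustment:** the site's 12-month baseline adherence, wave/region and care setting.

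Report the crude correlation as descriptive only. Study engagement delivered through Boost under Aim 3.

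This changes analysis wording only, because the variables are already planned for collection. The costs are a shorter exposure window and no Aim 2 estimate for Boost-delivered engagement. It does not remove unmeasured differences, such as more motivated sites both engaging and improving, so the result remains an association.

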### Data collection and analysis

Data collection will rely primarily on observational EMR data extracted from approximately 250 Intermountain Health sites, encompassing all pediatric encounters for indicated acute respiratory tract infections where antibiotics were prescribed during the study period. Baseline data from the 12 months prior to implementation will establish pre-intervention prescribing patterns, and ongoing EMR data abstraction will capture antibiotic selection, duration, and encounter-level covariates. Statistical analyses will follow a quasi-experimental pre–post design with staggered regional implementation, employing age, diagnosis, provider specialty, and care setting as covariates in linear probability models and using generalized estimating equations to account for clustering at the provider level. Clinic rurality and patient-level rurality, race, ethnicity, and preferred language may be controlled for if not deemed to be too collinear and not deemed as having too much missingness. The first three months of intervention will be considered an implementation rollout period and analyzed accordingly. Power calculations indicate > 99% power for a test at alpha = 0.05 to detect a ≥ 5% improvement in adherence across an estimated 356,000 encounters expected during the study period. If there is an overall effect, testing for each region separately will be conducted with Bonferroni-Holm adjustment for the three tests; if not significant, the region-specific tests will still be conducted but interpreted as exploratory.

Additional analyses will include interrupted time-series analysis and segmented regression to assess temporal trends, as in recent work [44]. Subgroup analyses will examine demographic covariates (e.g., ethnicity, language, insurance) and other characteristics (e.g., site rurality, setting type). Analyses will generally be conducted using robust variance estimators, unless explicit modeling of correlations is indicated (e.g., interrupted time-series analysis).

The Aim 3 analyses of Boost will proceed in an analogous manner, focusing on covariate-adjusted comparisons of adherence for encounters during the active implementation phase where Boost is in use to encounters during the active implementation phase where Boost is not in use.

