### Intermountain Health

Intermountain Health (IH) is a large, not-for-profit integrated health system in the Mountain West organized into three major geographic regions: Canyons (Central and Northern Utah, Idaho, and Western Wyoming), Peaks (Colorado, Eastern Wyoming, Montana, New Mexico), and Desert (Nevada, Arizona, & Southwest Utah). Each region includes urban, suburban, and rural communities (see Fig. 3 in Supplementary Information). This integrated structure with 33 hospitals and nearly 400 clinics has enabled IH to pursue ambitious system-wide quality improvement initiatives [32–36]. These attributes create a conducive environment for large-scale implementation of best practices, such as antibiotic stewardship, with support from leadership and alignment with system priorities. Prior and ongoing ambulatory antibiotic stewardship efforts in our system (see Table S2 and Fig. S4) demonstrated reductions in antibiotic prescribing for respiratory conditions in urgent care (UC) [23] and identified opportunities for improving prescription durations for common infectious conditions in primary care (PC) [29]. Other ongoing efforts seek to understand optimal strategies to increase the uptake of watchful waiting for pediatric ear infections [37, 38] and sustaining improvements in respiratory antibiotic prescribing in UC.

Despite these successes, prior outpatient stewardship activities at IH have been siloed – confined within particular service lines (UC or PC only, for example) or specific regions. A more coordinated and unified system-wide approach is needed to achieve substantial improvements in pediatric antibiotic prescribing, sustain them, and create a durable ambulatory antibiotic stewardship initiative in perpetuity that can adapt to external pressures as well as patient, provider, and pathogen changes along with evolving evidence.

In addition to its history of antibiotic stewardship, IH is well-positioned to undertake this project based on the following unique characteristics:A unified electronic health record (Epic) across all ambulatory and inpatient sitesAn established culture of best-practice implementation and continuous quality improvementSystem-wide infrastructure for implementing at scale including the Healthcare Delivery Institute, the Clinical Programs, and the Clinical Best Practice Integration (cBPI) model (see Fig. 1).

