### Primary innovation

Two complementary best practices will be tested: the primary outcome is adherence to recommended antibiotic *selection*.

Secondarily, we will examine adherence to recommended *duration*, as well as the combination of *selection and duration* (i.e., RADAR; see Fig. 5 in Supplementary Information). Prescriptions will be considered guideline-concordant if the antibiotic matches the recommendations in Table 1. Based on preparatory examination of data and charts, we will allow a 1-day window below or above the recommended duration (e.g., 4–6 days for 5 days).

**Table 1 Tab1:** Recommendations for selection and duration based on ARTI condition

Condition	Age	Antibiotic	Duration
Acute Otitis Media	6 months—2 years old	Amoxicillin	10 days
	2–5 years old		5 days
	> 5 years old		5 days
Sinusitis	< 18 years old	Amoxicillin	5 days
Group A strep Pharyngitis	> 6 months old	Amoxicillin or Penicillin	10 days
Community Acquired Pneumonia	> 3 months	Amoxicillin	5 days

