### Primary effectiveness and implementation outcomes

SCORE-Peds assigns value to both clinical effectiveness and implementation outcomes. Effectiveness outcomes will focus on improvements in guideline-concordant antibiotic prescribing for pediatric ARTIs.

The primary effectiveness outcome, which is the overall primary outcome with analyses as previously described, is the *antibiotic selection*– specifically the proportion of encounters in which a *narrow-spectrum antibiotic* is prescribed out of all ARTI encounters where any antibiotic was prescribed.

The primary implementation outcome will be two measures of *adoption* at the prescriber and site level. The measures of adoption are derivatives of the primary effectiveness outcome. Specifically, adoption is defined as the proportion of *prescribers* who have 80% adherence to antibiotic selection in their encounters, and the proportion of *sites* with 80% of prescribers considered adherent to antibiotic selection.

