### Other outcomes

Treatment failure will be examined as a balancing measure and defined as a return visit between 2 and 14 days for the same ARTI diagnosis where a new antibiotic prescription was given.

In terms of implementation, the study will evaluate the proportion of sites using clinical decision support tools (e.g., preference lists for antibiotic selection and duration), the percentage of clinicians engaging with audit-and-feedback dashboards, and indicators of implementation engagement such as attendance at trainings, and participation in site facilitation.

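### Treatment-failure return visits fall inside the primary denominator and are scored as if they were first-line prescribing decisions

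*Protocol article*

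**What the plan says.** All references are to the protocol article.

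- *Data collection and analysis* describes the extract as "encompassing all pediatric encounters for indicated acute respiratory tract infections where antibiotics were prescribed during the study period". It states no first-encounter-per-episode rule.
- *Primary effectiveness and implementation outcomes* sets the primary outcome as the proportion with a narrow-spectrum agent "out of all ARTI encounters where any antibiotic was prescribed". Adoption is derived from it: the proportion of prescribers with 80% adherence in their encounters, and the proportion of sites with 80% of prescribers adherent.
- *Primary innovation* gives the scoring rule: "Prescriptions will be considered guideline-concordant if the antibiotic matches the recommendations in Table 1". Table 1 has one recommendation per condition and age band, and no row for retreatment.
- *Other outcomes* defines treatment failure, the balancing measure, as "a return visit between 2 and 14 days for the same ARTI diagnosis where a new antibiotic prescription was given".
- *Secondary effectiveness outcomes* puts duration over all encounters with an antibiotic; the *Discussion* gives RADAR the same denominator.

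**The concern.** Every visit that meets the treatment-failure definition is also an ARTI encounter with an antibiotic, so it meets the primary denominator definition too. A clinician who sees a child after a failed first-line course and changes the agent is recorded as non-adherent to a table that does not address that situation. Whether changing the agent is good care is not at issue here; the point is what the measure counts.

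Two things are at stake. First, the level of adherence is understated, and by more for prescribers and sites that see more returns. Because adoption is a hard cut on each prescriber and Boost is directed at sites with lower adoption, patient flow can affect who is classed as a low adopter. Second, the balancing measure and the primary outcome are mechanically linked. If the share of return visits changes between periods, through the intervention, season or case mix, measured adherence changes even when first-line choice does not.

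**Working it through.** **Inputs.** From the document: the denominator, the scoring rule, the 2 to 14 day return definition, the 80% prescriber cut, 356,000 encounters, alpha 0.05, and power above 99% for a gain of at least 5%. Not in the document, and therefore assumed over ranges: baseline adherence, the return rate, and first-line use at return.

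**1. The plan's power figure.** With 178,000 encounters per period (a 1:1 split is assumed), two-sided alpha 0.05, 70% baseline and a 5-point gain, 99% power needs 2,926 encounters per period. The stated power therefore holds up to a design effect of about 178,000 / 2,926 = 60.8. The figure reproduces, so the issue is bias and not power. The difference detectable with 99% power is (1.960 + 2.326) × √(2 × 0.7 × 0.3 / 178,000) = 0.0066, or 0.7 points without clustering. It is 2.1 points at a design effect of 10 and 4.7 at 50.

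**2. Effect on the level.** Let p be index adherence, r the return visits per index visit, and f first-line use at return. Measured adherence = (p + r·f) / (1 + r).

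- p = 0.80, r = 0.02, f = 0.30: 0.806 / 1.02 = 79.0%
- p = 0.80, r = 0.08, f = 0.10: 0.808 / 1.08 = 74.8%

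**3. Effect on the prescriber cut.** For measured adherence to reach 80%, p must be at least 0.80 + r(0.80 − f).

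- r = 0.02, f = 0.30: 81.0%
- r = 0.08, f = 0.10: 85.6%

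So the index adherence needed to be counted as an adopter depends on how many return visits the prescriber sees.

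**4. Effect on the pre-post difference, constant return rate.** With r and f the same in both periods, a gain of 5 points in p is measured as 5 / (1 + r).

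- r = 0.02: 5 / 1.02 = 4.9 points
- r = 0.08: 5 / 1.08 = 4.6 points

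**5. Effect on the pre-post difference, changing return share.** Let s be return visits as a share of the denominator, with p = 0.70 and f = 0.20 in both periods. Measured adherence = 0.70(1 − s) + 0.20s = 0.70 − 0.50s.

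| s | Measured | Change from s = 5% |
|---|---|---|
| 5% | 67.5% | – |
| 3% | 68.5% | +1.0 points |
| 8% | 66.0% | −1.5 points |

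Both shifts exceed the 0.7 points detectable without clustering; both are below the 2.1 points at a design effect of 10.

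**6. Encounters that move to no antibiotic.** If a fraction d of treated encounters becomes untreated and those had adherence a, measured adherence = (p − d·a) / (1 − d). With p = 0.70 and d = 0.05:

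- a = 0.30: 0.685 / 0.95 = 72.1%, a shift of +2.1 points
- a = 0.70: no shift
- a = 0.90: 0.655 / 0.95 = 68.9%, a shift of −1.1 points

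The sign depends on a, about which the document says nothing.

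**The case against.** **Returns occur in both periods.** This stands for the pre-post comparison: under a constant return share the attenuation is only 0.1 to 0.4 points on a gain of 5. The comparison regions and the interrupted time series may also absorb changes common to all regions. Neither helps the level or the adoption cut, nor a change in return share specific to one region and period.

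**The limitation is acknowledged.** The *Discussion* says of RADAR that prior antibiotic history may be hard to capture and that justified deviations can be missed. But the treatment-failure measure cannot be computed without linking a visit to an earlier same-diagnosis visit, so the data needed to flag these visits are already required.

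**The treated-only denominator is deliberate.** The *Discussion* defends it for RADAR as measuring appropriateness rather than volume. That is a legitimate target and stands. A reader might infer from the caregiver education, and from the separate work to "increase the uptake of watchful waiting for pediatric ear infections", that adherence will fall because care improved. The document does not support a direction: removed encounters with below-average adherence would raise the rate (step 6). What remains is that inclusion depends on a decision the programme may influence, which merits a descriptive check.

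**Allergy exclusion.** The criterion reads "Children whose records include penicillin allergies will be excluded from evaluation" and gives no date. A reader might infer that labels acquired later remove earlier encounters and bias the balancing measure downwards. The document does not say that labels are applied backwards, and dating a record item is detail that a condensed article may leave to the full plan. No finding is made on it.

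**Conclusion.** The point holds on the stated wording: return visits that define treatment failure are also primary-outcome observations, and a changed agent at such a visit counts as non-adherence. The main consequence is for the level of adherence and for prescriber and site adoption. Under the assumed rates, 80% index adherence reads 1.0 to 5.2 points too low. The pre-post difference is only slightly attenuated if the return share is stable, and is biased by about 1 to 1.5 points under the assumed changes in share. None of these rates comes from the document, so the sizes are illustrations; the inclusion of return visits does follow from the text.

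A reader might take the 79.0% to 74.8% range as the programme failing its own 80% standard. It does not show that: the 80% cut applies to individual prescribers, and then to the share of adherent prescribers within a site. The document sets no 80% threshold for overall adherence. The power statement is unaffected. This should be corrected, but it does not undermine the design.

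**What to change.** Score selection, duration, RADAR and both adoption measures on index encounters only, defined as those with no antibiotic encounter for the same ARTI diagnosis in the preceding 14 days. Keep return visits for the balancing measure, and present the all-encounter version as a sensitivity analysis. The lookback is slightly wider than the treatment-failure window, since it also removes repeat antibiotic encounters less than 2 days apart; the plan should say so.

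Because inclusion requires an antibiotic, also run the query without that filter and report the antibiotic rate per ARTI encounter by period and region, as a check on composition shift with no presumed direction.

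The cost is one extra query and one table, and a few percent of encounters leave the primary denominator, which the power can bear. One caution: *Data management* dates the common EMR to September 2025. If visit linkage is less complete before then, fewer returns will be removed at baseline. The treatment-failure measure has the same dependence, and the all-encounter sensitivity analysis would help to show its effect.
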